### **Design**

This 4-arm RCT will compare the relative effectiveness and cost-effectiveness of process versus outcome-based financial incentives in improving LDL cholesterol in patients who are at high risk for CVD and have been prescribed statins. Adherence in all groups will be measured using an electronic pill container as a recording device. The intervention will consist of an active phase of 12 months followed by 6 additional months of observation. Participants will be randomized evenly into one of 4 arms. The primary outcome will be change in LDL cholesterol from baseline to 12 months. All participants will have LDL cholesterol checked at baseline, 3, 6, 9, and 12 months during the interventions, and at 18 months (without incentives, in order to assess the sustainability of the effects achieved by the incentives). We selected cholesterol for this study of process versus outcomes because a change in LDL depends on sustained adherence to a statin. LDL cholesterol is easily, inexpensively and objectively measured. The impressive degree of risk reduction associated with LDL lowering is well established. The interventions will consist of financial incentives lasting 12 months for arms 1, 3, and usual care (no incentives) for arm 4. The net value of incentive payments are equivalent in arms 1, 2 and 3. Participants in Process (arm #1) and the Process plus Outcomes (arm #3) groups will be eligible for an adherence-based sweepstakes. The expected value of the daily sweepstakes payments will be \$1.40 in the Process arm, and will be \$0.70 in the Process with Outcomes arm. Thus, participants in arms 1 and 3 may benefit from daily engagement and the opportunity for multiple, short-term rewards in changing adherence behavior. At months 3, 6, 9, and 12 every participant in the Outcomes (arm #2) and the Process with Outcomes (arm #3) interventions will be eligible for a payment (\$126 to arm #2; \$63 to arm #3) if the participants LDL has improved by 10 mg/dl compared to the LDL at the end of the previous quarter. The daily expected value of these rewards per day will be equivalent to each of the other intervention arms. Study sites. Participants in the study will be employees of corporations with CVS-Caremark pharmacy benefits (see letter of support from [name]) and Health System patients (Penn Medicine and Lancaster General Health (LGH)). The study will be run by UPENN investigators, who will communicate with participants through the Way to Health portal and by phone. Inclusion criteria. On further review of the recent AHA guidelines, we are changing our inclusion criteria to invite anyone with LDL190 (regardless of disease risk factors) as well as anyone with CAD with LDL100. The criteria includes: Individuals at high risk of a cardiac event, specifically one of the following: Individuals with clinical ASCVD (defined as diagnosis with myocardial infarction, stroke, or peripheral vascular disease) with an LDL greater than or equal to 100 mg/dl ; Individuals with Diabetes (between the ages of 40-75) with an LDL greater than or equal to 100 mg/dl; Individuals without clinical ASCVD or diabetes with LDLC with an LDL greater than or equal to 100 mg/dl and estimated 10-year ASCVD risk 7.5%; Individuals without clinical ASCVD or diabetes with LDL cholesterol 190 mg/dl A prescription filled for a statin medication within the last 12 months (derived from pharmacy records); Imperfect statin adherence level as defined by one of the following: Medication Possession Ratio (MPR) less than or equal to 80% A score 0 on the 8-item Morisky Medication Adherence Questionnaire completed during enrollment Exclusion criteria. Patients will be excluded if they 1) are younger than 18 years old; 2) have a contraindication to further statin use or have suffered statin side effects, such as myopathy; 3) will not or cannot give consent; 4) have a history of active or progressive liver disease are participating in another clinical trial with related aims, 6) have co-morbidities likely to lead to death within a short period (e.g. metastatic cancer), or 7) are prescribed by their doctor PCSK9 inhibitor injections coupled with statin therapy. Study Procedures Recruitment. All potentially eligible employees within the CVS-covered group will be contacted via existing communication channels through CVS. Potentially eligible employees will have evidence of diabetes medication use and/or CVD medication use in the CVS pharmacy database. These individuals will be sent letters (paper or email) describing the study and inviting them to enroll. Potentially eligible patients recruited from Penns Health system will be contacted by the study team via letter, email and phone calls. Baseline assessment

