
## Characteristics of the Study Population

### Target population

Study participants will be recruited by Penn Medicine (and LGH) or CVS Caremark on behalf of the health plans as a business associate. This study will recruit participants through employer partners of CVS Caremark who meet eligibility criteria including having diabetes and/or CVD as well as statin use with medication possession ratio 80%. We used CVS claims data starting 1/1/2010 to identify individuals likely to have diabetes (on the basis of diabetes medication use) and CVD (on the basis of a previously validated algorithm that is highly specific and that uses combinations of medications commonly prescribed to patients with CVD). The CVS database reveals that out of 2,030,494 overall statin users, a total of 179,963 are classified as having diabetes and an MPR for their statin of 80%, while 70,001 are classified as having CVD and a statin MPR80%. These individuals would therefore be potentially eligible for our study. The MPR was calculated over a 365 day period.

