
#### **Key inclusion criteria**

Individuals at high risk of a cardiac event, specifically one of the following: Individuals with clinical ASCVD (defined as diagnosis with myocardial infarction, stroke, or peripheral vascular disease) with an LDL greater than or equal to 100 mg/dl ; Individuals with Diabetes (between the ages of 40-75) with an LDL greater than or equal to 100 mg/dl; Individuals without clinical ASCVD or diabetes with LDLC with an LDL greater than or equal to 100 mg/dl and estimated 10-year ASCVD risk 7.5%; Individuals without clinical ASCVD or diabetes with LDL cholesterol 190 mg/dl A prescription filled for a statin medication within the last 12 months (derived from pharmacy records or EHR); Imperfect statin adherence level as defined by one of the following: Medication Possession Ratio (MPR) less than or equal to 80% A score 0 on the 8-item Morisky Medication Adherence Questionnaire completed during enrollment

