**Cost effectiveness analysis.** Measurement of costs and cost effectiveness. For our initial analysis, we will take a payer perspective. We will complete a within-trial analysis comparing incremental costs and incremental change in LDL in each arm, compared with control, during the 12 months of the trial. As a secondary analysis, we will substitute a societal perspective, which will include costs to patients, such as transportation and the time the patient devotes to the intervention. For both these analyses, costs will include: (1) incentive payments to participants (excluding incentives specific to the research); (2) costs of lab tests for those interventions in which lab tests are necessary to decide whether the participant has earned an incentive payment; (3) operational costs of implementing the interventions, including staff time administering the incentives and the computer platform to deliver the incentives (the Way to Health platform used in this study or an alternative that might be used by an employer); and (4) costs of the adherence measurement device (the electronic pill bottle and fees for connecting to the computer platform). We will also include the drug costs associated with statin medication use when adherence improves. Following usual practice in cost-effectiveness analysis we will conduct sensitivity analyses to assess the impact of uncertainty about these data, e.g., the standard error of the estimate of effectiveness, and to explore variations that might occur across employers. For the societal perspective cost-effectiveness analysis, we will follow the recommendations of the Second Panel on Cost-Effectiveness in Health and Medicine to compute additional costs to patients related to participating in an incentives program, including medication side effects, and time spent on the intervention, including travel and waiting time (using data from American Time Use Survey); time will

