be valued at appropriate wage rates. Long-term Effects of LDL Reductions on CVD Events and Cost-Effectiveness: The goal of lowering LDL is to prevent CVD complications. To estimate the cost and effectiveness associated with preventing cardiac outcomes, if our primary analyses of effectiveness indicate significant effects of the intervention, we will use a validated model of long-term cardiac risk, the Coronary Heart Disease (CHD) Policy Model. The CHD Policy Model is a computer-simulation, state-transition (Markov cohort) model of the incidence and prevalence of CVD (myocardial infarction, sudden death, revascularization, angina, stroke) and of the mortality and costs associated with these conditions in U.S. adults. The Model has been used to describe trends in CVD, project the effects of interventions to reduce CVD risk, and model the cost-effectiveness of interventions. [name], who leads the core modeling team, will adapt the Model to our study population, individuals with diabetes and/or known CVD. Based on decreases in LDL observed in the arms of this study, the Model will estimate the number and type of CVD events avoided, the quality-adjusted life years (QALYs) gained, and CVD treatment costs in each arm. We will use these estimates to calculate the cost-effectiveness of the intervention in each arm. Costs and health effects will be discounted 3% per annum. Return on investment: In addition to the cost-effectiveness analysis, if our primary analyses of effectiveness indicate significant effects of the intervention, we will conduct an analysis of potential return on investment for employers, the business case for preventing expensive health complications in the short- to medium-term. Using the CHD Policy Model we will estimate costs and savings of an incentives plan to the employer 3, 5, and 7 years after implementation. Savings will include reduced medical expenditures due to avoided CVD events and complications as well as increases in projected productivity as a result of reductions in CVD disability and death. Cost-effectiveness References 1. Peter J. Neumann, Gillian D. Sanders, Louise B. Russell, Joanna E. Siegel, Theodore G. Ganiats, editors, Cost-Effectiveness in Health and Medicine, second edition, New York: Oxford University Press, 2016. 2. Bibbins-Domingo K, Coxson P, Pletcher MJ, Lightwood J, Goldman L. Adolescent overweight and future adult coronary heart disease. *N Engl J Med* 2007;357:2371-9. 3. Odden MC, Coxson PG, Moran A, Lightwood JM, Goldman L, Bibbins-Domingo K. The impact of the aging population on coronary heart disease in the United States. *Am J Med* 2011;124:827-33 e5. 4. Lazar LD, Pletcher MJ, Coxson PG, Bibbins-Domingo K, Goldman L. Cost-effectiveness of statin therapy for primary prevention in a low-cost statin era. *Circulation* 2011;124:146-53. 5. Pletcher MJ, Lazar L, Bibbins-Domingo K, et al. Comparing impact and cost-effectiveness of primary prevention strategies for lipid-lowering. *Ann Intern Med* 2009;150:243-54. 6. Lightwood J, Bibbins-Domingo K, Coxson P, Wang YC, Williams L, Goldman L. Forecasting the future economic burden of current adolescent overweight: an estimate of the coronary heart disease policy model. *Am J Public Health* 2009;99:2230-7.

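### The long-term model is described for a diabetes/CVD cohort although people with neither condition are eligible, and no planned cost-effectiveness analysis directly compares the incentive arms with each other

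*Combined protocol and SAP*

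**What the plan says.** **Model population.** In the protocol's Analysis Plan, the part on long-term effects says the modelling team "will adapt the Model to our study population, individuals with diabetes and/or known CVD". The CHD Policy Model then supplies CVD events avoided, QALYs and treatment costs by arm, and also the employer return on investment at 3, 5 and 7 years. Both uses are conditional on significant effects in the primary effectiveness analyses.

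**Eligible population.** Key inclusion criteria list two routes that need neither disease: "Individuals without clinical ASCVD or diabetes with LDLC with an LDL greater than or equal to 100 mg/dl and estimated 10-year ASCVD risk 7.5" (a percentage), and "Individuals without clinical ASCVD or diabetes with LDL cholesterol 190 mg/dl". The comparison signs are missing from the text available to me; I read both values as lower limits. Design records the widening: "we are changing our inclusion criteria to invite anyone with LDL190 (regardless of disease risk factors". Target population still describes people recruited through the pharmacy-benefit employers as those "who meet eligibility criteria including having diabetes and/or CVD as well as statin use".

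**Comparators.** The within-trial cost-effectiveness analysis is defined as "comparing incremental costs and incremental change in LDL in each arm, compared with control, during the 12 months of the trial". For the long-term analysis the text says only "We will use these estimates to calculate the cost-effectiveness of the intervention in each arm", with no comparator named. Design presents the trial as a comparison of process and outcome incentives on cost-effectiveness as well as effectiveness. The SAP has no cost-effectiveness section.

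**The concern.** The LDL effect fed into the model comes from everyone randomised, while the cohort to which it is applied is described as a subset of them. Absolute events averted scale with baseline risk. If the people left out differ in risk from those kept in, events averted, QALYs, cost per QALY and return on investment describe a population other than the one enrolled.

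The second issue concerns the choice between programmes. The three incentive programmes are alternatives, so a payer must know whether a dearer one is worth its extra cost over a cheaper one. Separate ratios against usual care do not answer that. For LDL, the plan does compare incentive arms with each other (Step 2 of the power section under Accrual; Tukey comparisons in SAP section 2.1). For cost-effectiveness it describes no counterpart.

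**Working it through.** **No figure to reproduce.** The documents state no events averted, QALYs, cost-effectiveness ratio, case mix or average baseline risk. What follows shows what the result depends on; it does not estimate the bias.

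**1. Population mismatch.** Let f be the share of participants with neither condition, and r their baseline risk divided by that of participants with diabetes or CVD. Assume the same LDL change and the same relative event reduction in both groups. Then

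modelled / true events averted = 1 / [(1 − f) + f × r].

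Both f and r are assumptions:

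| f | r = 0.25 | r = 0.5 | r = 1 | r = 1.25 |
|---|---|---|---|---|
| 10% | 1.08 | 1.05 | 1.00 | 0.98 |
| 25% | 1.23 | 1.14 | 1.00 | 0.94 |
| 50% | 1.60 | 1.33 | 1.00 | 0.89 |

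For example, f = 25% and r = 0.25 give 1 / (0.75 + 0.0625) = 1.23.

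**2. The same in events.** The power section gives 5% fewer CVD events per 10 mg/dl. It is not stated to be a model input and is used here only for scale. Per 1,000 people over 10 years with a 10 mg/dl reduction:

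- modelled = 1,000 × 0.05 × R_H
- enrolled mix = 1,000 × 0.05 × [(1 − f) × R_H + f × R_L]

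R_H is the risk with diabetes or CVD and R_L the risk with neither. Both are assumed, with f = 25%:

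| R_H | R_L | Modelled | Enrolled mix | Ratio |
|---|---|---|---|---|
| 30% | 7.5% | 15.0 | 12.2 | 1.23 |
| 20% | 7.5% | 10.0 | 8.4 | 1.19 |
| 10% | 7.5% | 5.0 | 4.7 | 1.07 |
| 7.5% | 7.5% | 3.75 | 3.75 | 1.00 |
| 10% | 15% | 5.0 | 5.6 | 0.89 |

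The modelled figure is too high only when f > 0 and r < 1.

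**3. Is the omitted group likely to be trivial?** The share is not stated. The screen on diabetes or CVD medication applies to the pharmacy-benefit route (Target population, Accrual). SAP sections 1 and 2.1 name only Penn Medicine and Lancaster General as study populations, and Accrual says those patients are found through laboratory data in the medical record. So nothing suggests that the group is negligible. SAP section 2.2 plans a subgroup split by ASCVD status, but that does not separate diabetes from neither condition.

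**4. Incentive arms against each other.** The sweepstakes is worth 0.01 × $50 + 0.18 × $5 = $1.40 a day, as the protocol states. With full success over 12 months the incentive values are:

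- Process: $1.40 × 365 = $511
- Outcome: $126 × 4 = $504
- Combined: $0.70 × 365 + $63 × 4 = $507.50

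These are nearly equal by design. Cost differences between programmes must therefore come mainly from success rates and from the other listed costs: laboratory tests (counted only where a payment depends on them), devices and operations. The relevant quantity is (C_j − C_i) / (E_j − E_i) for adjacent programmes i and j ordered by cost. The two ratios (C_i − C_0) / (E_i − E_0) and (C_j − C_0) / (E_j − E_0) do not determine it. The separate increments do, but their uncertainties cannot simply be added, because both contain the same control arm.

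**The case against.** **The descriptor may be a leftover.** The main clause tells the modellers to use the study population, and Target population carries similar older wording. A careful modeller might use the enrolled mix anyway. This is a fair reading and it makes the problem easy to cure. It does not remove it, because no other text corrects the cohort.

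**Direction and size.** A reader might infer that events averted will be overstated and cost per QALY will look too favourable, by perhaps 14% to 60%. That range follows from an omitted share of 20% to 50% and a diabetes/CVD risk of 20% to 30% against 7.5%: 20 / (0.2 × 7.5 + 0.8 × 20) = 1.14 and 30 / (0.5 × 7.5 + 0.5 × 30) = 1.60. The arithmetic is right, but those shares and the 20% to 30% risks are not in the documents. Moreover, 7.5% is an entry limit and not a group average, the LDL 190 route has no stated risk criterion, and the diabetes route has no risk floor. The Abstract and Background do treat diabetes as equivalent in risk to CVD, which makes upward bias the more plausible direction without establishing it.

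**Comparators.** A reader might also infer that every economic analysis is against control only. That wording covers the 12-month analysis; the long-term comparator is simply missing. Further, Aim 4 asks for the cost-effectiveness of each intervention, which comparison with control meets, and between-arm point estimates can be recovered by subtracting increments. This stands, so it would be too strong to say that the trial could not show which incentive to buy. What remains is that Design promises the relative comparison and no analysis, with its uncertainty, is specified for it.

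**Conclusion.** The concern holds in a limited form. The model cohort as described leaves out two eligible groups, so modelled events averted, QALYs and return on investment may be biased. The bias is upward if those groups have lower baseline risk, nil if risk is equal, and downward if it is higher; the documents do not allow its size to be computed. It arises only if the primary analyses are significant, which is also when the modelled results would be used. The within-trial cost per unit of LDL change is not affected by the cohort mismatch.

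The comparator gap is separate and, for the within-trial analysis, does not depend on significance. No planned analysis directly addresses process-versus-outcome cost-effectiveness. Neither issue touches the primary LDL inference. Both are worth settling before the economic analysis is run.

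**What to change.** **Model cohort (Analysis Plan, long-term effects).** Replace the diabetes and/or CVD description with the enrolled case mix. Run the model in strata for ASCVD, diabetes, the 10-year-risk route and the LDL 190 route, and weight by the numbers enrolled. Use the same cohort for return on investment.

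**Comparators (Analysis Plan, within-trial and long-term parts).** State the long-term comparator. In both parts add a full incremental analysis across the four arms: order them by cost, remove dominated arms, and report each ratio against the next-cheapest remaining arm, or report net benefit with its uncertainty. Keep the comparison with control alongside.

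**Cost.** Revised wording and a few extra model runs; no new trial data for the incremental analysis. The cost per QALY may come out less favourable.

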
**The following documents are currently attached to this item:**

*There are no documents attached for this item.*

### **Data confidentiality**

- x **Paper-based records will be kept in a secure location and only be accessible to personnel involved in the study.**
- x **Computer-based files will only be made available to personnel involved in the study through the use of access privileges and passwords.**  
**Prior to access to any study-related information, personnel will be required to sign statements agreeing to protect the security and confidentiality of identifiable information.**
- x **Wherever feasible, identifiers will be removed from study-related information.**  
**A Certificate of Confidentiality will be obtained, because the research could place the subject at risk of criminal or civil liability or cause damage to the subject's financial standing, employability, or liability.**  
**A waiver of documentation of consent is being requested, because the only link between the subject and the study would be the consent document and the primary risk is a breach of confidentiality. (This is not an option for FDA-regulated research.)**
- x **Precautions are in place to ensure the data is secure by using passwords and encryption, because the research involves web-based surveys.**  
**Audio and/or video recordings will be transcribed and then destroyed to eliminate audible identification of subjects.**

## **Subject Confidentiality**

Research material will be obtained from participant interviews, the electronic pill containers adherence monitoring devices, and laboratory data from in-person blood draws for cholesterol lipid panel (including LDL). All participants will provide informed consent for access to these materials. The data to be collected include demographic data (e.g., age, sex, self-identified race), outcome data, adherence data (from the electronic pill container -if participants use the electronic pill bottle beyond the active phase of 12 months, we may analyze that adherence data), and medical conditions and medications. All measurements will be obtained according to the procedures outlined. Research material that is obtained will be used for research purposes only. The UPENN Biomedical Informatics Consortium (BMIC) will be the hub for the hardware and database infrastructure that will support the project and where the Way to Health web portal is based. The BMIC is a joint effort of the University of Pennsylvania's Abramson Cancer Center, the Cardiovascular Institute, the Department of Pathology, and the Leonard Davis Institute. The BMIC provides a secure computing environment for a large volume of highly sensitive data, including clinical, genetic, socioeconomic, and financial information. Among the IT projects currently managed by BMIC are: (1) the capture and organization of complex, longitudinal clinical data via web and clinical applications portals from cancer patients enrolled in clinical trials; (2) the integration of genetic array databases and clinical data obtained from patients with cardiovascular disease; (3) computational biology and cytometry database management and analyses; (4) economic and health policy research using Medicare claims from over 40 million Medicare beneficiaries. BMIC requires all users of data or applications on BMIC servers to complete a BMIC-hosted cybersecurity awareness course annually, which stresses federal data security policies under data use agreements with the university. Curriculum includes HIPAA training and covers secure data transfer, passwords, computer security habits and knowledge of what constitutes misuse or inappropriate use of the server. We will implement multiple, redundant protective measures to guarantee the privacy and security of the participant data. All investigators and research staff with direct access to the identifiable data will be required to undergo annual responsible conduct of research, cybersecurity, and Health Insurance Portability and Accountability Act certification in accordance with University of Pennsylvania regulations. All data for this project will be stored on the secure/firewalled servers of the BMIC Data Center, in data files that will be protected by multiple password layers. These data servers are maintained in a guarded facility behind several locked doors, with very limited physical access rights. They are also cyber-protected by extensive firewalls and multiple layers of communication encryption. Electronic access rights are carefully controlled by University of Pennsylvania system managers. We will use highly secure methods of data encryption for all transactions involving participants financial information using a level of security comparable to what is used in commercial financial transactions. We believe this multi-layer system of data security, identical to the system protecting the University of Pennsylvania Health Systems medical records, greatly minimizes the risk of loss of privacy.
